**Fig. 2 f0010:**
[figure not shown]
Stepped digital psychosocial intervention ICOnnecta’t.

The number of detected clinical cases: in the EG this will be obtained through the number of potential clinical cases recorded throughout treatment (VAS ≥6). In CG it will be obtained through the number of clinical cases recorded in the follow-up of face-to-face visits or if the patient reports a worsening by telephone and the visit is brought forward to confirm if it is a clinical case (VAS ≥6).

Waiting time to provide psychosocial intervention: In the EG, the time between the occurrence of a potential clinical case (VAS ≥ 6) and the start of psychosocial intervention will be assessed. The CG will assess the time between the face-to-face screening visit that confirms the clinical case and the next face-to-face visit.

Percentage of resolved psychosocial cases: in both groups it will be obtained through the number of clinical cases that are resolved.

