### Planned statistical analysis

2.9

Descriptive analyses will be performed using Student t or chi-squared tests, as appropriate. This will include assessment of sociodemographic and clinical variables at baseline, together with any pre-treatment differences between groups. Intention-to-treat analyses will then be performed through multilevel linear models to compare both groups on each primary outcome: emotional distress (HADS), demoralization (DS-II), QoL (FACT-L), and medication adherence (ARMS-e).

The modeling process will be parsimonious and guided by fit indexes, starting with a model using the time and type of therapy as fixed predictors. Then, random effects will be tested, and the interaction between time and type of therapy, the eHealth step reached, symptomatology (ESAS-r), and spirituality (FACIT-Sp) will be progressively entered as predictors. The estimation method will be maximum likelihood. Effect sizes (Hedges' g) will be reported for the primary outcomes and non-inferiority will be assessed for the HADS by comparing the means of both groups at T2 and T3. Additional multilevel linear models will be run to assess changes in health education (VAS) between groups, according to the same procedures. As for the cost-utility analyses, the EQ-5D will be used to compute the QALYs together with associated costs for medical care, psychotropics, sick leave, professional salaries, infrastructure, and transportation.

Descriptive analyses will also be conducted for platform's satisfaction and usability (VAS), as well as for participants reaching each step in the eHealth group. Mean differences in the number of clinical cases detected (according to the emotional thermometer), waiting time to provide care, and number of clinical cases solved will then be compared between groups by Student *t*-tests. For the reporting of results, 95 % confidence intervals will be provided. Analyses will be performed using IBM SPSS version 24 (IBM Corp., Armonk, NY, USA) and R software, with support provided by the biostatistics department of IDIBELL.

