The first limitation of this study is its focus on patients with advanced lung cancer. This may make it difficult to generalize the current findings to other cancer populations. However, given that it will cover a broad range of psychosocial needs that are shared by all cancer patients, it should be able to serve as a starting point for developing other end-of-life care programs, regardless of the underlying pathology. Other methodological weaknesses include the high risk of dropout and missing data with online questionnaires, especially in this delicate cancer population. To diminish this risk, we have shortened the 1-year follow-up used in similar programs to just 9 months. Also, a health psychologist will closely follow all included patients and help them to complete the online questionnaires by phone when needed. The online questionnaires are also structured so that they begin with the primary outcomes in anticipation that this might facilitate their completion, and in any case, they have been designed to last a maximum of 20 min. Finally, although online treatments are increasingly considered acceptable, age and digital literacy still dictate access to ICT, and by association, the study. To improve digital literacy, the first face-to-face visit will include a digital welcoming session and we will provide a technical support service to all patients, including a video tutorial about how to use the ICOnnecta't application.

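### Student t-tests on raw case counts and completed waits ignore time under observation and cases that never reach care; the bias depends on how far the arms differ in these respects

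*Protocol article*

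**What the plan says.** Section 2.9 names the test. It lists "Mean differences in the number of clinical cases detected (according to the emotional thermometer), waiting time to provide care, and number of clinical cases solved" as the quantities to be compared by Student t-tests. The intention-to-treat multilevel models in the same section are assigned to the primary outcomes, and similar models to health education, but not to these three quantities.

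Section 2.5.2.3 defines them:

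- **Count, eHealth arm:** "the number of potential clinical cases recorded throughout treatment", a case being a thermometer score of 6 or more.
- **Count, control arm:** "the number of clinical cases recorded in the follow-up of face-to-face visits", plus cases reported by telephone and confirmed at a visit that is brought forward.
- **Wait, eHealth arm:** "the time between the occurrence of a potential clinical case (VAS ≥ 6) and the start of psychosocial intervention will be assessed".
- **Wait, control arm:** "the time between the face-to-face screening visit that confirms the clinical case and the next face-to-face visit".

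The article gives no person-time denominator, censoring rule or competing-event rule for any of these. Section 1.1 states the related hypothesis as superiority of eHealth on time to detection, intervention and resolution. Section 2.7 assumes 25% dropout, with no split by arm.

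**The concern.** A t-test on raw counts treats a patient observed for one month and a patient observed for nine months as equally informative. If one arm is observed for less time, it shows fewer cases even when the true rate is the same.

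A t-test on waiting time can use only waits that have ended. A control case with no later visit, or an eHealth case whose intervention never starts, has no value, and the plan assigns none. An arm that leaves more cases without care need not show a longer wait.

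The claim at stake is that eHealth detects distress and provides care sooner. The waiting-time test bears on it directly. The count bears on it less directly, because the hypothesis concerns time and not number of cases.

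**Working it through.** The article states no figure for case counts or waits, so there is nothing to reproduce. The 152 patients in section 2.7 are sized on HADS. From the article come 76 patients per arm, 25% dropout, 9 months (about 39 weeks) of follow-up, and an average of seven control sessions 2-3 weeks apart (section 2.6.2). Case rates, exit splits and true waits are assumptions.

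**1. Counts when exit differs by arm.** If a fraction d of an arm leaves, evenly over 9 months, mean follow-up is 9 × (1 − d/2) months. With equal true rates, the ratio of mean counts equals the ratio of mean follow-up. Poisson counts were simulated with 76 per arm and 10,000 runs, tested at two-sided 5%.

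| Exit in the two arms | Mean months | Count ratio | t-test rejection at 0.1 / 0.2 / 0.4 cases per month | Rate test on person-time |
|---|---|---|---|---|
| 25% / 25% | 7.875 / 7.875 | 1.00 | 5.0% / 4.6% / 5.0% | 4.8-5.1% |
| 30% / 20% | 7.65 / 8.10 | 0.94 | 6.0% / 7.1% / 8.9% | 4.8-5.1% |
| 35% / 15% | 7.425 / 8.325 | 0.89 | 9.9% / 12.8% / 20.0% | 4.9-5.6% |

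Other assumed rates, and variation between patients, widen the ranges. At 20% against 30%, with 0.5 to 6 cases per patient, rejection is 5.5-10%. At 15% against 35% it is 8-10% with 1 case per patient. With 6 cases it is about 27% without variation between patients and about 12% with gamma variation (shape 2).

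**2. Counts when observation differs by design.** Seven sessions have six gaps: 6 × 2 = 12 weeks to 6 × 3 = 18 weeks. The eHealth thermometer is weekly over about 39 weeks. If control visits stop at that average course, visit-based observation covers 12/39 = 31% to 18/39 = 46% of the eHealth period before anyone drops out. The article does not say whether they stop there.

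**3. Waits.** Take an exponential true wait with mean m weeks and a competing exit hazard h. The mean among served cases is 1/(1/m + h), and the unserved share is h/(1/m + h). A 25% dropout over 39 weeks gives h = −ln(0.75)/39 = 0.0074 per week.

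| True mean wait | Mean among served | Unserved share |
|---|---|---|
| 1 week | 0.993 | 0.7% |
| 2.5 weeks | 2.455 | 1.8% |
| 4 weeks | 3.885 | 2.9% |
| 8 weeks | 7.554 | 5.6% |

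In this model the proportional shortening equals the unserved share, so it is about 1-6%. At four times the hazard, a true wait of 8 weeks is seen as 6.47 weeks, with 19% unserved.

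**The case against.** The strongest reply is that the damage to the count comparison needs a difference between arms that the article does not state. Dropout is a single 25%, and at 25% in both arms the t-test holds its error rate. This stands, so the size can only be given conditionally. A difference is nonetheless plausible: the trial is open-label, the arms differ in mode of delivery, and the control sessions may cover a shorter period.

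A reader might infer that planned attrition makes the waiting-time test blind to a large gap in access. For example, with 7-day mean waits and 5% against 25% of cases unserved, care by day 30 is 0.95 × 0.986 = 94% against 0.75 × 0.986 = 74%, and the t-test still rejects in only about 5% of trials. The article does not support that picture as a result of dropout. At a 7-day wait, 25% unserved would need h = 1/3 per week, about 45 times the hazard implied by the planned dropout. Even 5% would need about 7 times.

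A reader might also infer that 1 in 7 control cases has no wait because it falls at the last session. Seven is an average, an even spread of cases over visits is assumed, and the article does not say that a case confirmed at a planned last session receives no further visit.

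Nor does the Discussion's warning of "the high risk of dropout and missing data with online questionnaires, especially in this delicate cancer population" settle the matter. It concerns online questionnaires, whereas these outcomes come from the thermometer, visits and telephone contact. The same paragraph promises close follow-up by a health psychologist.

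Finally, handling of waits that never end is often left to an analysis plan, and none is shown. But section 2.9 fixes the test, so the objection here is to a stated choice.

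**Conclusion.** The point holds in a limited form. The stated t-tests suit neither a count over unequal observation nor a wait that may never end, and they fit poorly with a hypothesis framed as time to intervention.

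For counts, nothing is distorted if exit and observation are equal in the arms. A 10-point or 20-point difference in exit, both assumed, gives a spurious count deficit of 6% or 11% and rejection of about 6-10% or 8-20%. The figure of about 27% is an extreme that needs 6 cases per patient and no variation between patients. A shorter control observation period could matter more, if control visits do stop at the average course.

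For waits, the planned dropout alone has a small effect, about 1-6% for true waits of 1-8 weeks. It is larger if death, refusal or a last visit leaves more cases unserved in one arm, which the article does not quantify.

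These are secondary outcomes, and the HADS non-inferiority conclusion does not depend on them.

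**What to change.** Replace the t-tests in section 2.9 for these two outcomes:

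1. Analyse case counts per patient by negative binomial regression with log time under observation as offset, and define that time for each arm.
2. Analyse time from case to first care by time-to-event methods, censored at withdrawal or month 9, with death as a competing event and allowance for repeated cases in one patient.
3. Report, for each arm, the number of unserved cases and the proportion of all cases reaching care by fixed days, for example 7, 14 and 30.

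The cost is new wording, slightly more analysis and output less simple than a mean difference. Sample size and trial procedures do not change. The sponsor must confirm that dates of case, care, exit and death are recorded, because the article does not say so.

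The offset does not correct for weekly screening in one arm against visit-based detection in the other, or for exit related to distress. Both should be acknowledged when the results are interpreted.

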##### Level 1: screening and monitoring

2.6.1.1

Screening of potential emotional distress and monitoring of physical symptoms through a mobile application (ICOnnecta't App). Patients can spontaneously communicate their mood through a VAS emotional thermometer. In addition, a health psychologist will program a weekly assessment with the same thermometer, with a score ≥ 6 (10 indicating maximum distress) triggering a video consultation or phone call to assess the distress and explore any specific psychosocial needs. These sessions are also intended to accompany the patient throughout their cancer journey. Before a session, patients complete the HADS, and if both the HADS (≥ 10) and the psychologist's impression confirm clinically significant distress, the patient will be escalated to the next level. This adaptation of a stepped-care program used in oncology will be followed for escalation to the subsequent levels (Jansen et al., 2017).

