#### Treatment as usual - psychosocial face-to-face treatment

2.6.2

Patients in the control group will receive standard in-person psychosocial care delivered by a clinical psychologist. This will consist of an average of seven individual sessions, lasting 45–60 min each, with an inter-session spacing of 2–3 weeks. The clinical psychologist will provide the intervention based on individual meaning-centered psychotherapy for advanced cancer patients (Breitbart et al., 2012), aiming to help maintain or enhance the sense of meaning, peace, and purpose in the lives of patients with advanced cancer. Patients in this treatment arm will also have access to the educational materials of level 2 of the eHealth intervention, which will be provided in a freely accessible web portal for all patients and their families.

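### Waiting time is to be compared by Student t-tests, which conventionally assume equal variances; if the arms differ in both spread and number of waits, the p-value and 95% CI can be off in either direction, and an unequal-variance test is a cheap improvement

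*Protocol article*

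**What the plan says.** Section 2.9 (Planned statistical analysis) sets the test for three process outcomes, the second being waiting time: "waiting time to provide care, and number of clinical cases solved will then be compared between groups by Student" *t*-tests. It adds that "95 % confidence intervals will be provided". No unequal-variance version is named.

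Section 2.5.2.3 defines the wait separately by arm. In the eHealth arm, "the time between the occurrence of a potential clinical case (VAS ≥ 6) and the start of psychosocial intervention will be assessed". In the control arm it is "the time between the face-to-face screening visit that confirms the clinical case and the next face-to-face visit".

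Detection also differs by arm. Section 2.6.1.1 says that in the eHealth arm "a health psychologist will program a weekly assessment with the same thermometer", and patients may also report their mood spontaneously. In the control arm, section 2.5.2.3 counts "clinical cases recorded in the follow-up of face-to-face visits or if the patient reports a worsening by telephone". Section 2.6.2 gives the control sessions an "inter-session spacing of 2–3 weeks".

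Section 1.1 closes by expecting shorter time to appropriate care, and its hypotheses include a significant improvement in time to intervention with eHealth.

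**The concern.** Student's test estimates one variance from both arms together. That is harmless when the arms have equal numbers or equal variances. When both differ, the pooled standard error is wrong. It is too small if the smaller group is the more variable one, and too large if it is the less variable one.

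The design makes both conditions plausible. A control wait is tied to the gap until the next booked visit. An eHealth wait runs from a thermometer score to the start of an intervention. Nothing in the article suggests that these two processes share a variance. A wait exists only where a case was detected, and detection is weekly in one arm and tied mainly to visits in the other. Randomisation balances patients, not detected cases, and the number of detected cases is itself an outcome compared between arms.

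At stake is the interval behind a stated superiority hypothesis. It could cover less than 95%, so that faster access is claimed too readily, or more than 95%, so that a real gain is missed.

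**Working it through.** **Inputs from the article.** Student t-test and 95% interval (section 2.9); arm-specific waits (2.5.2.3); weekly thermometer in the eHealth arm (2.6.1.1); visits 2 to 3 weeks apart in the control arm (2.6.2); 76 randomised per arm (2.7). The alpha for this outcome is not stated, so two-sided 5% is taken as the counterpart of the 95% interval.

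**No figure to reproduce.** The article gives no SD, expected case count or sample size for waiting time. The 152 participants in section 2.7 belong to the HADS comparison. All counts and SDs below are assumptions.

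**Formula.** With group sizes n1, n2 and true SDs s1, s2:

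- pooled variance: sp² = [(n1−1)s1² + (n2−1)s2²] / (n1+n2−2)
- ratio of pooled to true standard error: r = √[sp²(1/n1+1/n2)] / √(s1²/n1 + s2²/n2)
- approximate true error of a nominal 5% test: 2[1 − Φ(1.96 r)]

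**Worked example: 50 against 25, smaller group with twice the SD (1 v 2).**

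- sp² = (49×1 + 24×4)/73 = 145/73 = 1.986
- variance used by the pooled test: 1.986 × (1/50 + 1/25) = 0.119
- true variance: 1/50 + 4/25 = 0.180
- r = √(0.119/0.180) = 0.81, so the true error is about 11%

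**Reversed: larger group with twice the SD (2 v 1).**

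- sp² = (49×4 + 24×1)/73 = 220/73 = 3.014
- variance used: 3.014 × 0.06 = 0.181; true variance: 4/50 + 1/25 = 0.120
- r = √(0.181/0.120) = 1.23, so the true error is about 1.6%

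**Simulation** (normal waits, no true difference, one wait per patient):

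| Waits per arm | Smaller group more variable | Smaller group less variable |
|---|---|---|
| 45 v 35, SD ratio 1.5 to 2 | 6.1% to 7.0% | 4.0% to 3.6% |
| 50 v 25, SD ratio 2 to 3 | 11% to 14% | 1.7% to 1.1% |
| 60 v 20, SD ratio 2 to 3 | 15% to 20% | 0.8% to 0.3% |
| Equal numbers, SD ratio up to 3 | about 5% | about 5% |

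With equal SDs the pooled test is also at about 5% for every split tried. Welch's test stays near 5% for normal waits in all these cases. With skewed (gamma) waits, over splits from 1:1 to 5:1, it ran from 4.7% to 6.1%.

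**Cost of Welch when variances are equal** (simulated power, Student v Welch):

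- 57 v 57: 79.1% v 79.1%
- 40 v 20: 78.6% v 77.8%
- 45 v 15: 78.9% v 76.8%
- 50 v 10: 78.7% v 73.4%

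**Limit of Welch.** If patients contribute repeat waits (assumed 30 patients with 3 each against 20 with 2 each, intraclass correlation 0.3), Welch's error is about 9.5% with equal SDs and 8.7% with SDs of 3 v 6. Student gives 9.6% and 18.3%.

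**The case against.** The article never says pooled or equal variance. Student may be meant generically, and the exact variant could sit in an analysis plan that is not shown. This is fair, but the article does name the test, and nothing in it commits to the unequal-variance form. Naming the variant settles the matter.

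The harm needs two conditions together, and the article gives a figure for neither. This stands. A reader might infer that the waits will be unequal in number as a matter of fact. The article supports this only as a likely consequence of how cases are detected. Weekly screening may yield more episodes without yielding two or three times as many patients with at least one. Control patients average seven sessions and can also report worsening by telephone. At a milder imbalance such as 45 against 35 the error is modest.

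A reader might also infer that the planned test inflates false claims of faster access. The article does not support that direction. If control supplies fewer waits and booked visits keep them in a narrow band (an SD of about 2 days if uniform over 14 to 21 days, an assumption), the smaller group is the less variable one and the pooled test is conservative.

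Finally, part of the case for unequal variances comes from the different clocks in the two arms. The article has no separate evidence on how variable the waits would be under a common definition.

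**Conclusion.** The point holds as a cheap improvement for one secondary outcome. Section 2.9 names a test whose usual form assumes equal variances, for waits that arise by different processes and exist only for detected cases.

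Under the assumed counts and SDs, the true error of a nominal 5% test runs from about 4% to 7% at mild imbalance, and from about 1% to 14% at 50 against 25. More extreme splits widen this range. The size rests on SDs and counts that the article does not give, the direction is unknown, and the problem essentially disappears if either the numbers or the SDs are equal.

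It does not touch the HADS non-inferiority analysis or the 152 participants. An interval with correct coverage would still compare two differently defined waits, among cases selected after randomisation. Those matters are separate and weightier than the choice of test variant.

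**What to change.** In section 2.9, for waiting time, replace Student's test with Welch's unequal-variance *t*-test and its interval. Alternatively, name a bootstrap or robust-variance interval that treats the patient as the unit of resampling or clustering; this also handles repeat cases within a patient, which Welch does not. Fix the choice in advance and do not make it depend on a preliminary test of variances.

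The change is a few words and needs no new data or patients. It is not entirely free. If variances are in fact equal, Welch loses 0.8 points of power at 2:1, 2.2 at 3:1 and 5.3 at 5:1, and nothing with equal numbers. It does not replace a decision on the unit of analysis or on a common definition of the wait.

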## Discussion

3

The current protocol describes a randomized controlled trial intended to examine whether a stepped-care, eHealth-based psychosocial intervention can effectively detect and address the psychosocial needs of patients with advanced lung cancer. We plan to conduct an open-label randomized controlled trial in two groups: one receiving an individualized online stepped-care psychosocial intervention, and the other group receiving an average of seven face-to-face visits with a clinical psychologist.

Patients with lung cancer are mostly diagnosed at advanced disease stages and have minimal prospect of cure. Such a scenario produces stress and psychological trauma for many patients, which in turn, affects their QoL (Liegey Dougall et al., 2017). Given that effective palliative care should improve the QoL of patients and their families, tackling their psychosocial needs in an efficient manner should be among the top priorities of comprehensive palliative care. Health education (Yu et al., 2022) and psychosocial care (Jansen et al., 2019) can both mitigate the emotional distress of a diagnosis and improve QoL among patients with lung cancer. However, the limited access to such care presents an important barrier (Travado et al., 2017).

The use of eHealth can overcome barriers requiring physical attendance at health centers with symptoms of fatigue, dyspnea, or pain (Rajapakse, 2021). As ICTs have emerged to deliver psychosocial interventions reliably to vulnerable patients with advanced cancer (Penedo et al., 2020), clinicians and researchers have begun to study techniques to deliver palliative interventions in an eHealth format (Chua et al., 2019; Gómez-Batiste et al., 2014). However, existing research has usually centered on physical symptoms, not the emotional and spiritual concerns of patients. Furthermore, patients benefit most from psychosocial interventions when they have elevated baseline emotional distress (Jansen et al., 2019; Medina et al., 2022; Nissen et al., 2021), stressing the importance of individualized strategies that allocate resources to patients with at-risk profiles.

The online, stepped-care ecosystem we propose has significant potential for therapeutic application in palliative care settings, with this being the first study in advanced lung cancer to consider a predominant psychosocial approach. In the proposed intervention, levels of care are scaled by the complexity and technological integration of screening and follow-up, based on evidence that psychosocial interventions are emerging as a solution to increase service coverage and improve efficiency.

Implementing an online care system that monitors and adapts to the changing needs of the patients at the end-of-life will promote personalized and responsive attention. If cost-utility is proven, health providers may cover more psychosocial needs. In addition to reaching more patients, the proposed eHealth ecosystem should contribute to improved patient empowerment, health literacy, and involvement in actions designed to improve health. By promoting greater access, this program will also promote equity (Ciria-Suarez et al., 2022) during the process of improving QoL.

The first limitation of this study is its focus on patients with advanced lung cancer. This may make it difficult to generalize the current findings to other cancer populations. However, given that it will cover a broad range of psychosocial needs that are shared by all cancer patients, it should be able to serve as a starting point for developing other end-of-life care programs, regardless of the underlying pathology. Other methodological weaknesses include the high risk of dropout and missing data with online questionnaires, especially in this delicate cancer population. To diminish this risk, we have shortened the 1-year follow-up used in similar programs to just 9 months. Also, a health psychologist will closely follow all included patients and help them to complete the online questionnaires by phone when needed. The online questionnaires are also structured so that they begin with the primary outcomes in anticipation that this might facilitate their completion, and in any case, they have been designed to last a maximum of 20 min. Finally, although online treatments are increasingly considered acceptable, age and digital literacy still dictate access to ICT, and by association, the study. To improve digital literacy, the first face-to-face visit will include a digital welcoming session and we will provide a technical support service to all patients, including a video tutorial about how to use the ICOnnecta't application.

